### Intervention description {11a}

*Group 1 –* Caries removal with a low-speed drill (control group):Initial periapical radiography (Children's Insight IP-01 Periapical – Carestream, Rochester, Nova York, EUA);Prophylaxis with a toothbrush and fluoride toothpaste (Colgate® Children [name], Nova York, EUA) and fluoride toothpaste (Herjos Prophylactic Paste, Vigodent, Rio de Janeiro, Brazil);Relative isolation with cotton roll (Dental Roller Cotton – Cremer, Santa Catarina, Brazil) and aspirator (Disposable Dental Sucker – SSPlus, Paraná, Brazil);Microbiological sampling with ear curette (Meyhoefer auricular n° 2 curette (ABC Instrumentos Cirúrgicos, São Paulo, Brazil) for standardization of volume of carious tissue;Removal of carious dentin with carbide burs (Carbide Drill No. 6 Spherical CA – Angelus, Paraná, Brazil) and manual instruments (Double Dentin Digger n° 17/18 - Millennium – Golgran, São Paulo, Brazil);Second microbiological sampling with ear curette (Meyhoefer auricular n° 2 curette (ABC Instrumentos Cirúrgicos, São Paulo, Brazil) for standardization of volume of carious tissue;Clinical inspection of texture of the remaining dentin with an exploratory probe (Eighth Exploration Probe – Golgran, São Paulo, Brazil), to check the absence of soft tissue;Restoration with glass ionomer cement (Ketac Molar EasyMix – 3M ESPE); andClinical inspection for signs of infiltration and radiographic follow-up immediately, 1 week, and 1, 3, 6, and 12 months after treatment.

*Group 2 –* Partial removal of carious tissue with the administration of Papacarie™:Initial periapical radiography;Relative isolation with a cotton roll and aspirator;Microbiological sample with otoscope curette to standardize the volume of carious tissue;Application of Papacarie™ (Fórmula e Ação, São Paulo, SP, Brazil) for 5 min, removal of carious tissue around lateral walls of the cavity with a noncutting curette and no removal of carious tissue on pulp floor (partial removal) [10];Washing of the cavity with water and drying with absorbent paper;Second microbiological sampling;Clinical inspection of texture of the remaining dentin with an exploratory probe, to check the absence of soft tissue;Restoration with glass ionomer cement (Ketac Molar EasyMIx 3M ESPE); andClinical inspection for signs of infiltration and radiographic follow-up immediately, 1 week, and 1, 3, 6, and 12 months after treatment.

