*Group 3 –* Partial removal of carious tissue with the administration of Papacarie™ and application of *Bixa orellana* extract (20% - seed extract diluted in mineral oil):Initial periapical radiography;Relative isolation with a cotton roll and aspirator;Microbiological sample with otoscope curette to standardize the volume of carious tissue;Application of Papacarie™ with *Bixa orellana* extract (20%) (Fórmula e Ação, São Paulo, SP, Brazil) for 5 min, removal of carious tissue around lateral walls of the cavity with a noncutting curette and no removal of carious tissue on pulp floor (partial removal) [10];Washing of the cavity with water and drying with absorbent paper;Second microbiological sample of remaining dentin with curette;Clinical inspection of texture of the remaining dentin with an exploratory probe, to check the absence of soft tissue;Restoration with glass ionomer cement (Ketac Molar EasyMIx 3M ESPE); andClinical inspection for signs of infiltration and radiographic follow-up immediately, 1 week, and 1, 3, 6, and 12 months after treatment.

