#### Radiographic evaluation

This is one of the primary outcomes of the study. The radiographic examinations will be carried out in the following manner: (1) periapical radiographs will be used as a diagnostic aid; (2) after the incomplete removal of the demineralized dentine and the temporary filling of cavity, a bitewing radiograph it will be taken to allow the analysis of the radiolucent zone (RZ), that is, the amount of demineralized dentine left; (3) immediately, 1 week, and 1, 3, 6 and 12 months, periapical and bitewing radiographs will be taken to analyze the integrity of the periapical area and the eventual changes in the RZ.

To obtain geometric standardization of films, bitewing film holders will be used. The images obtained before and after the treatment will be digitized by a ScanJet 6100 scanner Hewllet-Packard (OR, USA). The images will be stored in maximum-quality JPG format. The Imagelab software (version 2.3, SoftiumSistemas de Informatica, São Paulo, Brazil) will be used to analyze the images (equalize and subtract). Change in the density measurement of the RZ during treatment will be evaluated blind through digital subtraction of radiographic images in relation to the initial exams in the experimental periods (immediately, 1 week, and 1, 3, 6, and 12 months).

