#### Evaluation of time required for the procedure (secondary outcome)

The time required for each procedure will be measured using a digital stopwatch (Kenko, Hong Kong) in minutes and seconds from the onset of treatment until the complete removal of the carious tissue. The time will be recorded on a specific chart for analysis. The need or non-need for anesthesia will also be recorded.

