## Assignment of interventions: blinding

### Who will be blinded {17a}

The clinical evaluations of the carious tissue removal, as well as the microbiological and radiographic analyses, will be performed by examiners blinded to the treatments performed on each tooth. Only the researcher in charge of procedures will know to which group the participants belong.

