## Data collection and management

### Plans for assessment and collection of outcomes {18a}

Researchers will be previously trained to collect data and perform evaluations, according to the parameters described in outcome measures. The previously trained examiner will evaluate all cavities after the respective interventions and will test the hardness of the remaining dentin. For carious tissue to be considered removed, there must be an agreement between the operator and the examiner. To determine interexaminer agreement regarding the clinical and radiographic evaluations by examiners, the calculation of Kappa coefficients will be used at baseline and follow-up appointments. Interexaminer agreement must be greater than 85% (*K*>0.85) Firstly, the researchers responsible for the procedures will write the information in paper case report forms. Then, the data will be entered electronically in Excel datasets, in computers to which only the authors will have access.

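### Procedure time is stopped at full caries removal, which Groups 2-4 rule out by design, and the soft-tissue check in those arms does not exempt the pulp floor

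*Protocol article*

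**What the plan says.** Section {11a} of the protocol article assigns caries removal by drill to Group 1. Groups 2, 3 and 4 receive the papain gel, with excavation of the lateral walls only and "no removal of carious tissue on pulp floor (partial removal"). Under Radiographic evaluation, the film used to measure the radiolucent zone is taken "after the incomplete removal of the demineralized dentine and the temporary filling of cavity", which fits carious dentin being left on purpose.

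Three other rules bear on when removal counts as finished:

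- **Timing, a secondary outcome.** Each procedure is timed "from the onset of treatment until the complete removal of the carious tissue".
- **Probe check.** The lists for Groups 2-4 each include "Clinical inspection of texture of the remaining dentin with an exploratory probe, to check the absence of soft tissue". Apart from naming the probe's make, Group 1's step reads the same.
- **Agreement, section {18a}.** A trained examiner "will evaluate all cavities after the respective interventions and will test the hardness of the remaining dentin", and "For carious tissue to be considered removed, there must be an agreement between the operator and the examiner".

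On blinding, section {17a} states: "Only the researcher in charge of procedures will know to which group the participants belong".

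**The concern.** A time outcome needs a stop point that every arm can reach. Here one stop rule, full removal, covers all four arms, while three of them are told to leave carious tissue on the pulp floor. Whoever holds the stopwatch in those arms has to choose a substitute, and the article does not say which. The drill arm would then be timed to the written end point and the gel arms to an improvised one. Any difference in time would partly reflect that choice.

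The probe check raises a related problem. In Groups 2-4 the dentin that remains includes the floor nobody was allowed to excavate. If that floor is soft, the cavity fails the check because the operator followed the protocol. An operator who responded by excavating the floor would depart from the assigned intervention and work against the stated rationale in section {6a}, which is to make pulp exposure less likely.

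**Working it through.** No figure in the plan is at issue, so the check sets the rules side by side and then counts the teeth concerned.

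**1. Stop rule against assigned removal**

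| Arm | Carious tissue on the pulp floor | Can the written stop (full removal) be reached? |
|---|---|---|
| Group 1, drill | no restriction stated | yes |
| Group 2, gel | to be left | no |
| Group 3, gel and extract | to be left | no |
| Group 4, gel, extract and LED | to be left | no |

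This holds whether the floor is hard or soft, because the stop rule refers to carious tissue and not to soft tissue. No exception for the floor or for Groups 2-4 appears anywhere in the article.

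**2. Probe check against assigned removal**

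The check concerns softness, while the floor rule concerns carious tissue, and the two need not coincide. If the floor left behind is firm, both rules can be met. If it is soft, they cannot. The eligibility criteria enrol acute, active dentin lesions, so a soft floor is plausible, but the article does not say how often it will occur.

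**3. Agreement rule against assigned removal**

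The examiner assesses cavities after each arm's own intervention. The rule speaks of tissue considered removed, without saying that all of it must be, and sets no hardness threshold for the floor. It can therefore be read consistently with partial removal, although it does not say so.

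**4. Extent** (numbers per group from Sample size {14})

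- To be recruited: 3 × 40 = 120 of 4 × 40 = 160 teeth; 120/160 = 75%.
- At the stated minimum: 3 × 34 = 102 of 4 × 34 = 136 teeth; 102/136 = 75%.
- Not affected: Group 1, 1 × 40 = 40 teeth; 40/160 = 25%.

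**5. Group 4's irradiation**

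The one-minute irradiation is listed after the removal step. A clock that stops at the end of removal leaves that minute out, under the present wording and under the corrected one.

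**The case against.** The strongest reply is that the intended meaning is plain. The floor instruction is specific and repeated in all three gel arms, so a sensible operator would stop the clock when the assigned removal is done and would probe the walls. Procedure time is secondary and is not among the specific objectives in section {7}. A condensed article, citing other work for the technique, may also leave operating detail to the full protocol.

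Part of this stands. The practical reading is likely, and it keeps the point minor. It does not remove the point, because the article does not leave the stop open. It states one, and that one contradicts the intervention in three arms.

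A reader might infer more than the text supports:

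- **That the soft-tissue check cannot be passed in Groups 2-4.** This is not shown. The background section says that the gel softens dentin and also that it dissolves infected dentin, so the state of the floor at probing is unknown. The conflict is conditional on a soft floor.
- **That the protocol directs the operator to excavate the floor.** It does not. The check is an inspection, followed directly by restoration, and no step orders further removal after a failed check.
- **That the agreement rule in {18a} is a further contradiction.** It can be read in line with each arm's intervention.
- **That bacterial counts are biased.** Nothing in the article shows this. The second sample precedes the check, and that order is not criticised here.

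**Conclusion.** The point holds and is minor. The contradiction is certain for the timing outcome: its stop point is excluded by design in three of four arms (75% of teeth), so drill and gel times have no common end point as written. For the probe check it is conditional, arising only where the untouched floor is soft. The agreement rule in {18a} needs only a clarifying phrase.

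The conclusion assumes that the article's wording is what operators will follow. The size and direction of any effect on procedure time cannot be estimated, because the article gives no times. No effect on the CFU outcome is claimed.

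**What to change.** - **Time outcome:** define the stop as completion of the caries removal assigned to the arm, label the outcome removal time, and record Group 4's one-minute irradiation separately.
- **Section {11a}, Groups 2-4:** limit the soft-tissue criterion to the lateral walls. Group 1 stays as it is.
- **Section {18a}:** state that agreement concerns the tissue the arm requires to be removed. Section {17a} says of the assessors: "The clinical evaluations of the carious tissue removal, as well as the microbiological and radiographic analyses, will be performed by examiners blinded". The operator, who knows the arm, should therefore match the examiner's finding to the arm's requirement, so that the examiner need not be told the group.

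The cost is a wording correction in three places and one additional time entry in Group 4. Sample size, visits, randomization and the order of sampling do not change. Scoring walls and floor separately in every cavity, or repeating the sample if tissue is removed after the second one, would be optional refinements and is not needed to cure the defect.

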## Introduction

### Background and rationale {6a}

Antimicrobial photodynamic therapy (aPDT) is a promising new approach that aims to promote the reduction of microorganisms and it can be an innovative treatment to control oral biofilm microorganisms [1, 2]. Among these microorganisms, *Streptococcus mutans (SM)* and lactobacilli are usually present [1, 2]. Furthermore, it has been used in the treatment of dental caries [3]. Many studies have been conducted to confirm the effectiveness of this treatment modality [3–6].

The minimally invasive clinical treatment is considered an approach to the treatment of tooth decay, which acts on detection, diagnosis, interception, and treatment at the microscopic level. The partial removal of dental caries in order to maintain the integrity of the pulp is currently considered the treatment of choice for deep carious lesions, provided that some diagnostic principles are respected [7].

Currently, the treatment of these lesions is done with the removal of carious tissue using burs, hand excavators, or other techniques. Alternatively, chemo-mechanical caries removal agents can be used instead [8]. Papacarie ™ is considered a minimally invasive clinical treatment approach to treating dental caries with proven efficacy [3, 7–10]. It is a papain-based gel employing natural enzymes extracted from papaya husk that promotes the softening of the dentin. The gel acts upon the contaminated dentin and has an effect on local bacteria, as well as being biocompatible and having neutral pH [7]. However, it is necessary to improve its antimicrobial action. Clinical studies conducted to evaluate the antimicrobial potential of Papacarie™ (Fórmula e Ação, São Paulo, SP, Brazil) attribute its efficacy to its physical-chemical properties [8]. Partial caries removal by the Papacarie™ is capable of effectively dissolving the structure of caries-infected dentin through cysteine protease enzymatic action with additional bactericidal and anti-inflammatory properties [10].

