#### Specific objectives

To investigate the efficacy of photodynamic therapy with *Bixa orellana* and Papacarie™ with regard to microbiological (counting of colony-forming units before and after treatments – CFU), radiographic (integrity of the periapical area and eventual changes in the radiolucent zones), and clinical aspects (retention of the restorative material in the cavity and occurrence of secondary caries) (primary objective);To evaluate the antimicrobial effect of aPDT on caries-affected dentin in permanent teeth (secondary objective);To perform a radiographic evaluation of the remaining dentin and radiographic density at 6 evaluation times, over a 12-month period (secondary objective); andTo evaluate the need for local anesthesia during intervention and the degree of pain/discomfort (with a face scale) of children during the different procedures (secondary objective).

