*Group 4 –* Partial removal of carious tissue with the administration of Papacarie™, application of *Bixa orellana* extract (20%) and LED (aPDT):Initial periapical radiography;Relative isolation with a cotton roll and aspirator;Microbiological sample with otoscope curette to standardize the volume of carious tissue;Application of Papacarie™ with *Bixa orellana* extract (20%) for 5 min and the light-emitting diode (LED) light curing device (Valo Cordless Ultradent®, South Jordan, UT, USA) an office appliance, with a coupled radiometer, and a spectrum of 440–480 nm will be used. Both the volunteer to be treated and the professional will be using specific eye protection glasses. The active end of the LED will be coated with clear disposable plastic (PVC), thus avoiding cross-contamination. Removal of carious tissue around lateral walls of the cavity with a noncutting curette and no removal of carious tissue on pulp floor (partial removal) [10–12];Irradiation of dental tissue for 1 min on a single point;Washing of the cavity with water and drying with absorbent paper;Second microbiological sample of remaining dentin with curette;Clinical inspection of texture of the remaining dentin with an exploratory probe, to check the absence of soft tissue;Restoration with glass ionomer cement (Ketac Molar EasyMIx 3M ESPE); andClinical inspection for signs of infiltration and radiographic follow-up immediately, 1 week, and 1, 3, 6, and 12 months after treatment.

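### Group 4 has a 1 min irradiation before washing that Group 3 does not match, so the only contrast that isolates the light also differs in contact time with the gel and extract

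*Protocol article*

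**What the plan says.** Intervention description {11a} in the protocol article lists each group's steps in order.

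- **Group 3** (gel plus extract, no light): the mixture is applied "for 5 min, removal of carious tissue around lateral walls of the cavity with a noncutting curette", and the pulp floor is left. The list then continues "partial removal) [10];Washing of the cavity with water and drying with absorbent paper;Second microbiological sample of remaining dentin with curette". No wait or light-off step is listed.
- **Group 4** (gel plus extract plus LED): the mixture is applied for the same nominal time, in a sentence that also introduces the device: "extract (20%) for 5 min and the light-emitting diode (LED) light curing device". Excavation is described as in Group 3. The next item is "Irradiation of dental tissue for 1 min on a single point", and only after it come washing and the second sample.

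Specific objectives includes this aim: "To evaluate the antimicrobial effect of aPDT on caries-affected dentin in permanent teeth (secondary objective"). Outcomes {12} makes the microbiological evaluation one of the primary outcomes. It compares colony-forming units before treatment with those in the remaining dentin afterwards.

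On the gel without light, Background and rationale {6a} states: "The gel acts upon the contaminated dentin and has an effect on local bacteria". The same section describes the dye as antimicrobial, separately from its possible role as a photosensitizer.

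**The concern.** Group 1 is drilling and Group 2 is gel without dye. Groups 3 and 4 are the only pair that differ by the light, so the antimicrobial contribution of irradiation has to be read from that pair. A light-off control serves this purpose when it differs from the active arm in the light alone. Here it also differs in the time the mixture can stay in the cavity before it is washed out and the remaining dentin is sampled.

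On the article's own description that time need not be inert. If the mixture keeps killing bacteria without light, the extra minute lowers Group 4 counts even when irradiation does nothing, and the error runs in favour of photodynamic therapy. Randomization and blinded assessment do not remove it, because the difference is part of how the arms are defined.

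**Working it through.** **Steps side by side** (Intervention description {11a}):

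| Step | Group 3 | Group 4 |
|---|---|---|
| Gel plus 20% extract applied | 5 min | 5 min |
| Lateral walls excavated, pulp floor left | t min, not stated | t min, not stated |
| Irradiation | none | 1 min |
| LED set-up | none | s min, not stated |
| Washing, then second sample | yes | yes |

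No rinse is listed before irradiation in Group 4, so washing is the first listed step that would clear mixture from the pulp floor in either arm.

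**Time from application to washing**, assuming the same excavation time in both arms:

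- Group 3: 5 + t
- Group 4: 5 + t + 1 + s = 6 + t + s
- Difference: 1 + s, so at least 1 min
- Ratio with s = 0: (6 + t)/(5 + t)

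The article gives no value for t, so a range is assumed:

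- t = 0: 6/5 = 1.20
- t = 2: 8/7 = 1.14
- t = 5: 11/10 = 1.10

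The ratio falls as t grows, so 1.20 is the most the stated minute can produce. Set-up time brings the ratio back to 1.20 only if 1 + s is at least 0.2 × (5 + t), that is, if s is at least 0.2t. The article gives no set-up time.

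**Effect on counts.** The article gives no kill rate for the mixture in the dark. The following is illustration only. Suppose the light has no effect, the outcome is compared by a two-sample t-test at two-sided 5%, and the extra contact shifts the outcome by an assumed fraction of its standard deviation (SD). The Group 3 v Group 4 test then rejects in:

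| Assumed shift | 40 per group | 34 per group |
|---|---|---|
| 0 | 5.0% | 5.0% |
| 0.1 SD | 7.3% | 6.9% |
| 0.2 SD | 14.3% | 12.8% |
| 0.3 SD | 26.3% | 23.0% |

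Nothing in the article ties any of these shifts to one minute of contact. The table shows how the error rate would respond to a shift, not that a shift of a given size occurs.

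**The case against.** The case for leaving this alone has several parts.

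- **The dark effect may be slight.** Background and rationale {6a} says the gel's antimicrobial action needs improving, and the Discussion says that in some studies its antibacterial effect is less than clear. No section says that killing continues beyond the fifth minute. This stands and limits the likely size, although the dye is called antimicrobial without such a reservation.
- **Little mixture may remain.** Excavation comes before the extra minute and may carry much of the gel away. The article does not say how much stays on the pulp floor. This also stands as a limit on size.
- **The light might fall within the 5 min.** The Group 4 application sentence names the LED in the same breath as the application time. However, irradiation is a separate later item, after excavation and before washing. If the authors meant otherwise, the Group 4 list still needs correcting.
- **The contrast is not the trial's main aim.** The general objective, the primary objective and the hypothesis concern gel and photodynamic therapy in combination. The antimicrobial effect of aPDT is a secondary objective, and the Statistical methods section singles out no Group 3 v Group 4 test. This is correct and lowers the stakes. The objective is nevertheless stated, its measure is a primary outcome, and no other pair of arms isolates the light.

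A reader might go further and infer that contact is 20% or more longer in Group 4, or that a Group 4 advantage could not be credited to photodynamic action at all. The article supports neither. The 20% figure leaves excavation time out of both totals and is a ceiling for the stated minute. An extra minute of unknown effect is a possible partial confounder and does not make the contrast uninterpretable.

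**Conclusion.** The asymmetry is real as the steps are listed. Any mixture remaining on the pulp floor acts about 1 min longer in Group 4 than in its only light-off comparator, a ratio of (6 + t)/(5 + t), at most 1.20 before LED set-up time. A lower post-treatment count in Group 4 than in Group 3 therefore cannot be fully separated from longer contact.

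The direction of the bias favours photodynamic therapy. Its size is unknown from the document. The conclusion rests on three assumptions: the steps are carried out in the listed order, some mixture survives excavation, and it retains some activity without light. The third is in line with the article's own description. The second is plausible because the pulp floor is not excavated, but it is not stated. This is an inexpensive improvement to the design and not a defect that invalidates the trial.

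**What to change.** Reconcile the Group 3 and Group 4 step lists in Intervention description {11a} so that the interval from application of the mixture to washing is the same in both arms. One way is a light-off hold in Group 3, placed before washing and matched to the irradiation step, including device positioning. This review does not propose any contact or irradiation time; that is for the investigators to set.

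The planned recruitment window was 30 May 2022 to 30 April 2023 and the article appeared on 4 March 2023, so many participants may already have been treated as listed. For them, the report should say that Group 3 v Group 4 compares light plus longer contact with neither. If the sequence is changed part-way, the two versions of the Group 3 procedure should be identifiable in the data.

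The cost is one line of text and about a minute of chair time per Group 3 participant, for at most 40 children. The procedure-time outcome is not affected, because its stopwatch stops once carious tissue removal is complete, before any such hold would begin.
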